## **PROJECT PROPOSAL**

### **Role of Adjuvant Yoga Therapy in Managing Withdrawal Symptoms of Patients with Opioid Use Disorder**

#### **Introduction:**

Opioid use disorder is characterized by chronic use of opioids such as heroin, morphine, codeine, fentanyl, and synthetic opioids like oxycodone which causes clinically significant impairment. It involves an intense desire to use opioids, increased opioid tolerance, and withdrawal syndrome when discontinued. Opioid use disorders affect over 16 million people worldwide and over 120,000 deaths worldwide annually occur due to opioids.(1)

Withdrawal from opioids is characterized by specific problematic behavioral change, with physiologic and cognitive components. The opioid withdrawal syndrome is a collection of clinical signs and symptoms such as hypertension, tachycardia, insomnia, mydriasis, piloerection, lacrimation, excessive sweating, rhinorrhoea, yawning, nausea, vomiting and diarrhea, anxiety, shivering, body aches, easily agitated, craving, hyperactivity, rapid breathing.(2,3) The time course of withdrawal is dependent on the half-life of the opioid used; it may last from 5 to 14 days.(2)

World health organisation recommended three medication treatment for withdrawal symptoms.(4) They are 1) opioid receptor full agonist methadone, 2) opioid receptor antagonist naltrexone 3) opioid receptor partial agonist buprenorphine (available as sublingual or buccal tablets or films, a skin patch). Patients treated with Buprenorphine experienced less severe withdrawal when compared with other drugs(5). Although buprenorphine is an ideal drug of choice, it alone does not control withdrawal symptoms, so ancillary medications such as clonazepam (sedative-hypnotics) for anxiety, trazodone and zolpidem (act via GABA) for sleep, ibuprofen (NSAID) for muscle cramps, bismuth subsalicylate for diarrhea, Ondansetron and prochlorperazine for nausea and vomiting are also used in the management of withdrawal symptoms.(6)

Sleep disturbance is common and often severe during opioid withdrawal. Sleep disturbance includes reduced total sleep time, continuity and quality which causes poor treatment outcomes.(7) Sleep and substance use are found to be interrelated, there is a lot of sleep disturbance evident in patients with opioid use disorder before and after treatment.(8) Sleep and substance use are found to be interrelated, there is a lot of sleep disturbance evident in patients with opioid use disorder before and after treatment. There is limited research in understanding HRV changes during the withdrawal phase which shows a significant decrease in cardiac vagal tone following naloxone administration in opioid-dependent participants.(9) Pain is one of the risk factors for increased severity of withdrawal symptoms.(10) Buprenorphine is found to be effective in managing pain-related symptoms well when compared with other drugs.(11) Opioid withdrawal is also associated with anxiety and other symptoms related to sympathetic outflow which are usually treated with drugs such as lofexidine and clonidine(12).

Opioid partial agonist buprenorphine peak of action is 30-60 min and has a duration of action up to 72 hrs. for high doses.(13) Increasing dose of buprenorphine may produce typical side effects such as constipation, insomnia, weight gain, hormonal changes, cardiac arrhythmias

etc.(5) Buprenorphine is a costly drug and not easily accessible, it is only available at designated Opioid Substitution Therapy (OST) centres.

Yoga as an adjuvant could be an effective treatment for early recovery from various withdrawal symptoms. Yoga involves a combination of physical postures (asanas), breathing exercises (pranayama), meditation and relaxation. Evidence suggests that yoga could be effective in treating various withdrawal symptoms such as sleep disturbance, anxiety, body aches, craving, agitation, etc. Yoga effectively improves total sleep duration and sleep quality.(14) Yoga affects mood and improves the quality of life in patients suffering from substance use disorder, which is usually low in them when compared with the normal population.(15) Yoga could show improvement in symptoms like pain and anxiety immediately after the yoga session.(16) Studies suggest a reduction in anxiety in practitioners of yoga doing yoga at least once a week for 6 weeks.(17) Yoga has an effect on the autonomic nervous system several studies suggest an increase in parasympathetic activity in individuals practicing yoga.(18) A validated yoga module has been developed and found to be feasible, safe and potentially useful in reducing withdrawal symptoms and cravings of opioid use disorder patients.(19)

In the current study, we hypothesize that Yoga as an add-on therapy will show a significant form of recovery from withdrawal symptoms of opioid use disorder when compared to treatment only group.

#### **Aim:**

To study the impact of Yoga as an add-on therapy in recovery from withdrawal symptoms and autonomic regulation of opioid use disorder when compared to standard treatment alone.

#### **Objectives:**

- Primary objective:
  1. To evaluate the effect of Yoga on time to recovery from opioid withdrawal symptoms in patients with OUD using the and Clinical Opiate Withdrawal Scale (COWS) and heart rate variability parameters reflecting autonomic regulation.
- Secondary objective:

To access the changes following clinical measures in yoga as an add-on therapy group when compared with the standard treatment-alone group.

  1. Anxiety (HAM-A)
  2. Sleep latency
  3. Brief Pain Inventory

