#### **Hypothesis:**

- Null Hypothesis:

Yoga as an add-on therapy won't show a significant form of recovery from withdrawal symptoms of opioid use disorder and improved autonomic regulation when compared to treatment only group.

- Alternate Hypothesis:  
Yoga as an add-on therapy will show a significant form of recovery from withdrawal symptoms of opioid use disorder and improved autonomic regulation when compared to treatment only group.

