### **Assessments:**

- Clinical Opiate Withdrawal Scale (COWS)

- Heart Rate Variability (HRV)
- Hamilton anxiety rating scale (HAM-A)
- Brief Pain Inventory (BPI)
- Sleep Latency
- Yoga performance assessment (YPA)

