**Statistical analysis:**

- Data would be analyzed using R statistical software (Version 4.4.1). Based on the distribution and variance appropriate statistical tests will be used for analysis.
- Baseline continuous data will be analyzed using an independent sample t-test. Baseline categorical data will be analyzed using the chi-square test. Data will be checked for normality, for longitudinal analysis, a linear mixed model will be used.
- If the data is not normally distributed and the samples are small, a nonparametric test is appropriate, and to compare two groups Mann Whitney U test is performed.

- Primary longitudinal outcomes will be analyzed using Linear Mixed-Effects Models (LMM) with the lme4 package.
- Time to recovery from withdrawal symptoms will be analyzed using survival analysis.

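### The primary objective joins recovery on COWS with an unnamed set of HRV parameters, and the protocol does not settle which result decides the trial

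*Protocol*

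**What the plan says.** - **Objectives.** There is one primary objective: the effect of yoga on time to recovery from withdrawal, measured with COWS and "heart rate variability parameters reflecting autonomic regulation". Anxiety, sleep latency and pain are secondary.
- **Assessments.** HRV is listed as a single item. No index is named there, under Objectives or under Statistical analysis.
- **Introduction, Aim and Hypothesis.** The hypothesis that closes the Introduction concerns recovery from withdrawal only. The Aim adds autonomic regulation. The alternate hypothesis reads "Yoga as an add-on therapy will show a significant form of recovery from withdrawal symptoms of opioid use disorder and improved autonomic regulation", and the null hypothesis has the same joint form.
- **Statistical analysis.** "Primary longitudinal outcomes will be analyzed using Linear Mixed-Effects Models (LMM) with the lme4 package", and, as a separate item, "Time to recovery from withdrawal symptoms will be analyzed using survival analysis". The section also says "Based on the distribution and variance appropriate statistical tests will be used for analysis" and keeps the Mann-Whitney U test as an alternative.
- **Study design.** Assessments take place at baseline and at the end of the two-week intervention. The protocol does not define recovery on COWS.
- **Methodology.** 60 patients, 30 per arm. No significance level, power or effect size accompanies this figure.

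**The concern.** A primary objective should let a reader say, before the data are seen, which result makes the trial positive. Here the text supports at least three rules: COWS recovery alone (Introduction), COWS and HRV together (Aim and Hypothesis), or success on any primary measure (the analysis section simply lists tests). The same data could be positive under one rule and negative under another.

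Two further freedoms add to this. The HRV set is plural and unnamed, so the index can be chosen after the results are known. The mixed model is assigned to primary longitudinal outcomes in general, so it may or may not be a second test of COWS beside the survival analysis. At stake is an error rate above the nominal level under some rules, and a loss of power under another.

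**Working it through.** **Inputs.** From the protocol: COWS and HRV are the only primary measures; the two analyses are as quoted; there are 30 patients per arm. Assumed, because the protocol is silent: two-sided 5% per test; k = 2 to 5 HRV indices; independence unless stated otherwise. The protocol gives no overall error rate, so there is no figure of its own to reproduce.

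**Rule 1: any one success counts, no true effect anywhere.** With m independent tests the chance of at least one false positive is 1 − 0.95^m.

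| Tests | m | False-positive rate |
|---|---|---|
| 1 COWS + 2 HRV | 3 | 1 − 0.95^3 = 14.3% |
| 1 COWS + 5 HRV | 6 | 1 − 0.95^6 = 26.5% |
| 2 COWS + 2 HRV | 4 | 1 − 0.95^4 = 18.5% |
| 2 COWS + 5 HRV | 7 | 1 − 0.95^7 = 30.2% |

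The first two rows apply if the mixed model serves HRV only; the last two if COWS is tested by both analyses.

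Correlation lowers these rates. Simulation with normal test statistics (400,000 draws) gave:
- 1 COWS + 2 or 5 HRV, all pairwise correlations 0.5: 12.5% and 20.6%.
- 2 COWS + 2 or 5 HRV, correlation 0.5 within each measure and independence between them: 17.3% and 25.7%.
- The same with within-measure correlation 0.8: 15.0% and 19.6%.

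**Rule 2: COWS and HRV must both succeed.**

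*No true effect on either.* The error is the product of the two rates. With one COWS test it runs from 0.05 × 0.0975 = 0.5% (k = 2) to 0.05 × 0.2262 = 1.1% (k = 5). With two COWS tests it runs from 0.0975 × 0.0975 = 1.0% to 0.0975 × 0.2262 = 2.2%. This is small.

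*COWS truly improves, HRV does not.* The joint claim is then false in its HRV half. If any of k indices may supply that half, its chance is at most 1 − 0.95^k, and it reaches that value when the COWS test is certain to succeed:
- k = 2: 9.75%
- k = 3: 14.3%
- k = 5: 22.6%

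With 80% power on COWS (assumed) and independence, the k = 2 and k = 5 values become 0.8 × 9.75% = 7.8% and 0.8 × 22.6% = 18.1%. At correlation 0.5 among the indices, the upper limits for k = 2, 3 and 5 are about 9.1%, 12.5% and 18.2%.

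*Power.* If one COWS test and one HRV test each have 80% power (assumed) and are independent, joint power is 0.8 × 0.8 = 64%.

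**Rule 3: COWS recovery alone, one test.** The error is 5% by construction. This holds only if one COWS analysis is fixed in advance.

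**The case against.** The strongest reply is that the formal hypotheses use a conjunction. On that reading one significant test is not enough, and the error with no true effect on either measure is at most about 2%. This stands as far as it goes. A reader might infer from the list of tests that any single significant result would make the trial positive, but no passage says so, and the Hypothesis section points the other way. Nor does the conjunction settle the matter: the Introduction names recovery alone, and the joint rule still leaves the HRV index open.

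A reader might also infer that COWS has two competing primary analyses. The protocol never assigns the mixed model to COWS. Survival analysis for time to recovery and a mixed model for HRV is a coherent reading. The two-COWS-test rows above are therefore conditional.

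Third, the significance level, multiplicity method and test order are commonly left to a statistical analysis plan. One may exist; none was available for this review. Their absence is not the point here. The identity of the primary outcome belongs in the protocol, and the protocol's own statements of its hypothesis disagree. Two co-primary outcomes are a legitimate design, but then each must be named and the rule stated.

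Finally, a reader might infer that permitted ancillary drugs and nicotine make HRV an unsuitable primary measure. The documents do not show this. They give no effect of such drugs on HRV, patients are randomised, and other medication is documented in both arms. The point does not rely on that argument.

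**Conclusion.** The concern holds in this form: the protocol leaves the primary outcome and the success rule indeterminate. Under an any-success rule the false-positive rate would be about 14% to 26% with one COWS test, or about 19% to 30% with two. Under a both-must-succeed rule the error with no true effect is small, but a false joint claim is possible in up to about 10% to 23% of trials when only COWS improves, and joint power is lower than for either test alone (64% in the example).

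These sizes rest on an assumed two-sided 5% level, 2 to 5 indices and independence; correlation reduces the error rates. The indeterminacy itself needs none of these assumptions. It follows from comparing the Introduction, Aim, Objectives, Hypothesis and Statistical analysis sections.

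**What to change.** Before any unblinded analysis:

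1. Name COWS withdrawal as the single primary outcome, with one primary test that the assessment schedule supports. With assessments at baseline and end of intervention only, that is a baseline-adjusted comparison of end-of-intervention COWS between arms. Keep time to recovery as primary only if COWS is recorded repeatedly during the two weeks and recovery is defined in advance.
2. Label the other COWS analysis supportive, and state which outcomes the mixed model serves.
3. Move HRV to secondary with one named index. Label the remaining indices exploratory.
4. Align the hypothesis in the Introduction, the Aim, the primary objective and the formal hypotheses with that choice.

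**Cost.** With the end-of-intervention comparison the change is to wording only. Keeping time to recovery as primary is a design change if COWS is not already recorded between the two assessments, because it then needs added assessments as well as a definition of recovery. In either case HRV can no longer carry a primary claim.

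If the sponsor prefers to let either COWS or one named HRV index carry the claim, splitting the assumed 5% equally (2.5% each) raises the difference detectable with 30 per arm at 80% power. By the normal approximation it goes from (1.960 + 0.842) × √(2/30) = 0.72 SD to (2.241 + 0.842) × √(2/30) = 0.80 SD.

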#### **Hypothesis:**

- Null Hypothesis:

Yoga as an add-on therapy won't show a significant form of recovery from withdrawal symptoms of opioid use disorder and improved autonomic regulation when compared to treatment only group.

- Alternate Hypothesis:  
Yoga as an add-on therapy will show a significant form of recovery from withdrawal symptoms of opioid use disorder and improved autonomic regulation when compared to treatment only group.

### **Methodology:**

- Age: 18 to 50 years.
- Sex: Both male and female.
- Sample size: 60 (30 patients in Yoga + Treatment as usual group and 30 patients in treatment only group).
- Source of Subject: Inpatient services run by the CAM & Department of Integrative Medicine, National Institute of Mental Health and Neurosciences (NIMHANS), Bengaluru, India

### **Inclusion criteria:**

- Diagnosis of Opioid use disorder.
- Subjects with mild to moderate severity of withdrawal symptoms (Clinical Opiate Withdrawal Scale: COWS scores between 4 - 24).
- Subjects who got admitted into CAM, NIMHANS and started treatment with Buprenorphine.
- Age range: 18 to 50 years.
- Both genders.
- Written informed consent.

### **Exclusion criteria:**

- COWS score more than 25.
- Patients not willing to give informed consent.
- History of current medical illness that may significantly affect brain functions
- Patients with intractable pain due to other diseases and those on prescribed opioids for the pain of other medical conditions
- Impaired general intellectual functioning (Mini-Mental Status Exam, MMSE below 24).
- Past history of head injury or concomitant severe medical conditions.
- With co-morbid (alcohol/benzodiazepine/cannabis or multiple) substance dependence except nicotine.
- Prior exposure to specific yoga or other mind-body practices for OUD within past 6 months.
- Pregnant or post-partum subjects.

### **Assessments:**

- Clinical Opiate Withdrawal Scale (COWS)

- Heart Rate Variability (HRV)
- Hamilton anxiety rating scale (HAM-A)
- Brief Pain Inventory (BPI)
- Sleep Latency
- Yoga performance assessment (YPA)

### Study design:

Patients diagnosed with opioid use disorder are assessed for severity of withdrawal symptoms using Clinical Opiate Withdrawal Scale (COWS). The patients with mild to moderate severity of withdrawal symptoms and taking buprenorphine for management of symptoms are randomized into two groups that is Yoga + standard treatment group and Treatment only group. Duration of intervention is 2 weeks. Clinical history will be done at baseline. Assessments will be done at the baseline and at the end of the intervention, for those who are willing to participate in the study. Safety assessments and adverse events will be monitored and appropriately documented for the duration of study period. The medications prescribed and taken by the patients other than buprenorphine will be documented in both the groups during the study period.

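### Time to recovery is to be analysed by survival methods, but the readable protocol text assesses patients only at baseline and at two weeks, so recovery times are not observed

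*Protocol*

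**What the plan says.** Four places in the protocol bear on this.

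- **Objectives, primary objective:** "To evaluate the effect of Yoga on time to recovery from opioid withdrawal symptoms in patients with OUD", measured with COWS and with "heart rate variability parameters reflecting autonomic regulation".
- **Statistical analysis:** "Time to recovery from withdrawal symptoms will be analyzed using survival analysis". A separate line reads "Primary longitudinal outcomes will be analyzed using Linear Mixed-Effects Models (LMM) with the lme4 package".
- **Study design:** "Duration of intervention is 2 weeks", and "Assessments will be done at the baseline and at the end of the intervention". Between those points the section follows only safety and adverse events, and medications other than buprenorphine.
- **Introduction:** the withdrawal course depends on the half-life of the opioid used, and "it may last from 5 to 14 days".

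The Assessments section lists COWS but gives it no schedule of its own. The Schematic representation follows the Study design text, but its figure is not available here.

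**The concern.** A time-to-event analysis needs to know when each patient recovered, at least to within a short interval. The text provides one look after baseline, at about day 14. By the protocol's own account, withdrawal may be over anywhere from day 5 to day 14, so most of the information on speed of recovery lies where nobody is looking.

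The timing comparison in the primary objective is at stake. If yoga brings recovery forward by several days but both arms have recovered by day 14, the recovery-time analysis shows no difference. A statistical analysis plan cannot repair this, because no method recovers times that were never recorded.

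**Working it through.** **Inputs from the protocol.** 30 patients per arm (Methodology); two assessments 14 days apart (Study design); withdrawal lasting 5 to 14 days (Introduction); entry at "COWS scores between 4 - 24" (Inclusion criteria). The protocol gives no alpha, power, hazard ratio or recovery rate with the sample size of 60, so there is no figure of its own to reproduce. The assumptions below are mine and serve as illustration.

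**Step 1: what each patient contributes.** A patient recovered at the second assessment has a recovery time known only to lie after day 0 and up to day 14. A patient not recovered is right-censored at day 14. Every event shares the same interval, so the survival curve in each arm has one step.

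**Step 2: what the log-rank test becomes.** With N = 60, equal arms, d recoveries in total and r in the yoga arm, all at one time:

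- observed minus expected = r − d/2
- variance V = d × ½ × ½ × (60 − d)/59
- statistic = (r − d/2)² / V

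This is the uncorrected chi-square for two proportions multiplied by 59/60. If d = 60, then V = 60 × ¼ × 0/59 = 0 and there is no test.

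**Step 3: the extreme case.** Suppose control patients recover evenly over days 5 to 14 and yoga patients over days 5 to 10, all by day 14. In 2,000 simulated trials, daily ratings gave log-rank power of about 0.95. The two-assessment schedule gave zero variance, hence no test, in every trial.

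**Step 4: less extreme cases.** Assume a hazard ratio of 2 for recovery, 30 per arm and two-sided 5%. If a proportion p of controls has recovered by day 14, the yoga proportion is 1 − (1 − p)². Expected events are D = 30p + 30[1 − (1 − p)²]. The Schoenfeld approximation for observed times is power = Φ(ln 2 × √(D/4) − 1.96).

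| Control recovered | Yoga recovered | D | Observed times, formula | Daily ratings, simulated | Day-14 status, single-step log-rank | Day-14 status, Fisher |
|---|---|---|---|---|---|---|
| 80% | 96% | 24 + 28.8 = 52.8 | Φ(0.56) = 0.71 | about 0.71 | 0.53 | 0.29 |
| 90% | 99% | 27 + 29.7 = 56.7 | Φ(0.65) = 0.74 | about 0.74 | 0.28 | 0.06 |
| 95% | 99.75% | 28.5 + 29.9 = 58.4 | Φ(0.69) = 0.75 | about 0.74 | 0.06 | 0.003 |

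The two day-14 columns are exact: they sum binomial probabilities over all outcomes that the test rejects. Simulated values vary by one or two points between runs.

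**Step 5: sensitivity.** With exponential recovery times, control medians of 5 to 14 days and hazard ratios of 1.5 to 2.5, approximate power runs from 0.22 to 0.93 with observed times and from 0.21 to 0.77 with day-14 status. The gap is small when recovery is slow (median 14 days, hazard ratio 2: 0.56 against 0.52). It is large when recovery is fast (median 5 days, hazard ratio 2.5: 0.93 against 0.51).

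**The case against.** **The schematic may hold more visits.** Its figure cannot be read here, and its absence is not an error in the plan. The conclusion therefore applies to the readable text. If the schematic shows interim COWS ratings, it conflicts with the Study design section and the two must be reconciled. This stands as a qualification.

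**Time to recovery is not the whole primary objective.** A reader might infer that the trial cannot answer its primary question at all. The protocol does not support that: the objective also names HRV, and a linear mixed model covers the primary longitudinal outcomes. Baseline and two-week values allow pre-post comparisons of COWS and HRV. Only the timing part fails.

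**The loss of power depends on the test.** Pricing the loss with Fisher's exact test would give 0.29 at 80% control recovery. The protocol does not name that test, and it is conservative here. The single-step log-rank keeps 0.53, so the loss due to the schedule is about 0.71 − 0.53 = 18 points, not 42.

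**The recovery criterion may sit elsewhere.** No COWS cut-off for recovery is stated, which might look like a second defect. An exact event definition is commonly left to the statistical analysis plan, so it is not counted as one. Nor must patients qualify as recovered at entry: a criterion of COWS below 4 avoids that.

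**Early leavers.** A reader might infer that they supply nothing after baseline. Adverse events and other medications are documented during the study period, and the text is silent on an assessment at exit. What could be lost is efficacy data.

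**Routine ward charting** might supply interim scores, but the protocol does not provide for it, and unscheduled ratings need not be comparable between arms.

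**Conclusion.** The point holds. Under the readable text, time to recovery is named in the primary objective and given a survival analysis, but the schedule records only recovery status at about day 14. This conclusion rests on the protocol's own statements and not on the power figures.

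The size of the loss does rest on assumptions. With a hazard ratio of 2, 30 per arm and two-sided 5%, power on day-14 status is 18 points below that of daily ratings at 80% control recovery (0.53 against 0.71). The gap is 46 points at 90% (0.28 against 0.74) and 68 points at 95% (0.06 against 0.74). It is small if recovery is slow, and if all patients have recovered by day 14 there is no test. The mixed-model comparisons of COWS and HRV are unaffected. Correction is needed before patients are followed, because missed ratings cannot be collected afterwards.

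**What to change.** Choose one of two routes.

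1. **Keep time to recovery.** In Study design, schedule repeated COWS ratings, for example daily, from randomisation to day 14 or discharge, on the same schedule in both arms. Take randomisation as time zero. State, in the protocol or the statistical analysis plan, a recovery criterion below the entry floor of 4, so that no eligible patient counts as recovered at entry. Specify a discrete-time or interval-censored analysis, which suits ratings made once per interval.
2. **Keep two assessments.** Delete time to recovery from the primary objective and the survival analysis from the Statistical analysis section. Restate the outcome as COWS at two weeks, adjusted for baseline.

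In either case, check the schematic against the revised text.

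The first route uses an instrument already listed and needs no extra patients. Its cost is a modest rating workload: at most about 60 × 14 = 840 short ratings if done daily. The second costs only wording, but gives up the question of speed of recovery.
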